**【Over-the-counter drug】**
OTC drugs indicated for constipation, diarrhea, or abdominal pain

**Tests/treatments prohibited during the study period**
1. Enemas (use of enemas during the study period without bowel movements after two doses of rescue medication falls under the category of prohibited concomitant medications)
2. Defecation
3. Gastrointestinal endoscopy

#### Dose reduction and withdrawal criteria

2.6.3

If a subject experiences diarrhea (BSFS 6 or 7), the dose of linaclotide will be reduced to 0.25 mg once daily; if diarrhea persists after the dose reduction, the drug will be withdrawn as directed by the principal investigator or sub-investigator.

#### Dose escalation and resumption criteria

2.6.4

During the treatment period, the dose can be increased again to 0.5 mg in cases where it had been reduced to 0.25 mg once daily. If the subject experiences at least one BSFS type 1 to 5 during the withdrawal period, linaclotide will be resumed the following day, as directed by the principal investigator or sub-investigator.

### Discontinuation of research on individual subjects

2.7

The study will be discontinued in study subjects when any of the following criteria are met:

(1) when it is judged difficult to continue the study due to the occurrence of adverse events and ischemic colitis, or inflammatory bowel disease is suspected after administration; (2) when the subject requests discontinuation of participation in the study; (3) when it is impossible to continue the study due to the subject's circumstances, such as no longer coming to the hospital, moving, or being too busy; (4) when the subject does not meet the criteria for initiation of treatment within 28 days of enrollment, or when it is found after the start of treatment that the subject does not meet the eligibility criteria or he/she meets the exclusion criteria, and it is determined that continuation of the study is inappropriate; (5) when the subject's disease worsens or the improvement with the study drug is insufficient and the principal investigator or sub-investigator determines that the subject is not suited to the treatment; and (6) pregnancy after the start of treatment.

### Observation and handling of adverse events

2.8

In the event of an illness, the principal investigator or sub-investigator will take appropriate measures to ensure the safety of the study subjects, including discontinuation of treatment and administration of the study drug. If treatment is necessary, the investigator will inform the study participants of its need. If an adverse event is continued even at the last observation at the end of the study period, the investigator or sub-investigator continues to follow up until clinical stability or return to the baseline state is achieved.

### Evaluation items

2.9

Efficacy after switching from MgO to linaclotide will be evaluated using the JPAC-QOL scale.

The defecation satisfaction score is a 4-point scale (satisfactory, somewhat satisfactory, somewhat unsatisfactory, and unsatisfactory) that indicates the subject's level of satisfaction upon defecation.

The severity score of each abdominal symptom (abdominal distention, pain, and discomfort) will be evaluated on a 5-point scale (1: none, 2: weak, 3: moderate, 4: strong, and 5: very strong).

The severity of constipation is rated on a 5-point scale (0: none (no symptoms of constipation), 1: mild (slight symptoms of constipation), 2: moderate (constipation, but not severe), 3: severe (severe constipation and difficulty in defecating or only a slight feeling of defecation after going to the toilet), and 4: extremely severe (stubborn constipation, almost no defecation, or little or no sensation of defecation when going to the toilet)).

Stool shape (BSFS) will be evaluated on a 7-point scale (1: hard and colicky rabbit droppings (difficult to defecate); 2: sausage-like but bumpy (lumpy); 3, sausage-like with cracks on the surface; 4, smooth and soft sausage-like or snake-like with a coiled surface; 5, soft and semi-soft stools with distinct ends; 6, irregularly shaped small pieces of stool with loose edges and squishy, muddy stools, and 7: watery, liquid stools with no solids).

Straining in stool will be evaluated on a 5-point scale (1: not at all, 2: a little, 3: moderately, 4: a lot, and 5: extremely).

### Endpoints

2.10

#### Efficacy endpoints

2.10.1

The primary endpoint is the change from baseline in terms of the JPAC-QOL total score after 12 weeks of treatment. The secondary endpoints are listed in Table 4.

**Table 4 tbl4:** Study endpoints.

Study endpoints	
**Primary endpoint**	**Secondary endpoints**
Change in JPAC-QOL score from baseline at 12 weeks of linaclotide treatment	1. Change in weekly average of SBM frequency
	2. Percentage of subjects with SBM within 24 h of first dose
	3. Time to first SBM
	4. Change in weekly average of CSBM frequency
	5. Percentage of subjects with CSBM within 24 h of first dose
	6. Change in weekly average of stool forms
	7. Average weekly change in abdominal bloating severity score
	8. Average weekly change in abdominal pain and abdominal discomfort severity score
	9. Average weekly change in severity score of straining
	10. Change in JPAC-QOL overall score and subscale scores
	11. SF-12v2 summary score, change in subscale
	12. Satisfaction score on defecation

#### Safety assessment

2.10.2

Safety endpoints include adverse events that occur in the study subjects as a result of their participation in the study. Adverse events are all unwanted or unintended injuries or illnesses or signs thereof (including abnormal laboratory values) that occur in the study subjects, regardless of any causal relation. This includes any exacerbation of a pre-existing condition (not including the underlying disease) during the study period. The investigator or principal investigator will evaluate the extent, causal relationship, and severity of the adverse events following the Common Terminology Criteria for Adverse Events v5.0.

A “serious illness” is defined as any of the following: (1) death; (2) diseases that may lead to death; (3) diseases that require hospitalization or prolonged hospitalization for treatment; (4) disability; (5) diseases that may lead to disability; (6) diseases that are as serious as (3) through (5) above and diseases that may lead to death; and (7) congenital diseases or anomalies in later generations.

### Eligibility for analysis

2.11

The population to be analyzed is defined as follows: the primary analysis population is the full analysis set (FAS). FAS is defined as all patients enrolled in the study receiving at least one dose of linaclotide and showing at least one efficacy endpoint measured after baseline.

Additionally, the target population (per-protocol set: PPS) that meet the study protocol is defined as those subjects in the FAS who complied with the following criteria: (1) primary endpoints are available. (2) Inclusion criteria are met. (3) Exclusion criteria are not met. (4) The medication initiation criteria are met. (5) The study drug is administered for at least 42 days from the start of treatment or the day following the start of treatment. However, if the primary reason for discontinuation is “inadequate response” or “worsening of the target disease,” even if less than 42 days elapsed, the subject will be considered for PPS. (6) The drug compliance rate, excluding drug withdrawal during the treatment period, is at least 5/7 × 100%. (7) No rescue treatment or prohibited concomitant treatment is administered during the treatment period. (8) No prohibited tests are performed during the treatment period.

The safety analysis set (SAS) is defined as the population enrolled in the study who received the study drug at least once.

### Statistical analysis

2.12

Efficacy analyses will be performed using FAS. The results of the statistical tests will be interpreted according to the FAS; PPS will be used to assess the robustness of the results based on the FAS. The primary endpoint is the change in the JPAC-QOL total score from baseline at week 12. A paired *t*-test will be performed at a two-sided significance level of 5% for the change in the JPAC-QOL total score between the baseline and week 12. Additionally, the point estimation and 95% confidence intervals for the mean change will be calculated.

As secondary analyses, subgroup analyses will be performed for the following factors:(1)Abdominal symptoms (with or without abdominal symptoms)(2)Gender (male, female)(3)Age (<65 years, ≥65 years)

The secondary endpoints are presented in Table 4. Summary statistics of the measured values and changes from baseline will be calculated for each time point for items 1, 4, and 6–11. Paired t-tests will be performed on the amount of change, and 95% confidence intervals for differences will be calculated. For items 2 and 5, the number and percentages of subjects as well as the 95% confidence interval will be calculated. For item 3, a Kaplan-Meier curve will be plotted, and the median and 95% confidence interval of the time to event will be calculated. The earliest discontinuation, failure to observe, and expiration during the observation period will be defined as censoring. For item 12, the number and percentages of patients in each category will be calculated at each time point.

For safety analysis, the number of cases and percentages of adverse events and adverse events that cannot be denied as related to the study drug will be calculated. For the measurable parameters in the clinical laboratory tests, summary statistics of the actual measured values and changes from baseline will be calculated for each time point using descriptive statistics. For countable parameters, a frequency tally will be performed at each assessment time point. A shift table of the laboratory measurement abnormalities observed at each time point from the baseline compared to the normal range during the treatment period will be recorded.

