### Sample size estimation

2.4

The target number of cases in the study is 64. Of these, 32 subjects with abdominal symptoms and 32 without abdominal symptoms will be recruited. This is an exploratory study owing to the lack of data on the Japanese version of the Patient Assessment of Constipation Quality of Life questionnaire (JPAC-QOL) with linaclotide administration. In addition to the primary objective of evaluating the drug response in the overall population, the secondary objective is to evaluate the effectiveness in subgroups based on abdominal symptoms (with and without). The number of patients in each subgroup will be set to ensure 90% statistical power when a paired *t*-test is used at a two-sided significance level of 5% for assessing the change in the JPAC-QOL total score between the baseline and 12 weeks after treatment. A 90% power for each subpopulation will ensure that the main analysis, or the analysis for the total population, has a power of 90% or more if the effect size assumed for each subpopulation is correct. A long-term study of elobixibat in patients with chronic constipation showed that the mean age was 43.9 years and the mean change (standard deviation) in the JPAC-QOL overall score from baseline to week 12 was −0.69 (0.68) [8]. We will consider equivalent or better efficacy of a long-term study of elobixibat as clinically meaningful and set a target number of patients. Miller et al. reported that age is inversely correlated with baseline JPAC-QOL total scores [9]. Considering that the average age of the patients in this study is expected to be approximately 60 years, and assuming a 33% decrease in the mean change in the JPAC-QOL responses and no changes in the standard deviation, the mean change in the JPAC-QOL overall score from baseline to week 12 was assumed as −0.46 (0.68). Under this assumption, 25 subjects would be needed in each subpopulation to detect a significant change from baseline in the JPAC-QOL total score at week 12, with a power of 90% or greater. Assuming a 20% dropout rate during the study period, the target number of patients in each subpopulation in this study is 32. Therefore, the overall target number of cases is calculated as 64.

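### As written, the primary paired t-test can use only FAS patients with a week-12 JPAC-QOL score; poor responders may leave before then, and neither the FAS definition nor the PPS check guards against the resulting bias

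*Protocol article*

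**What the plan says.** All references are to the protocol article.

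- **Test (section 2.12).** The primary analysis is a paired t-test that "will be performed at a two-sided significance level of 5% for the change in the JPAC-QOL total score between the baseline and week 12", with a point estimate and 95% CI for the mean change. Efficacy is interpreted on the FAS, and the PPS serves to assess robustness.
- **FAS (section 2.11).** It contains enrolled patients "receiving at least one dose of linaclotide and showing at least one efficacy endpoint measured after baseline". Any efficacy measure qualifies, so a patient can be in the FAS without a week-12 JPAC-QOL score.
- **PPS (section 2.11).** Criterion (1) requires the primary endpoint to be available. Criterion (5) requires at least 42 days of treatment, but still considers patients who stopped earlier mainly for inadequate response or worsening.
- **Discontinuation (section 2.7).** The study, not only the drug, ends for the subject. Criterion (5) applies when the disease worsens or "the improvement with the study drug is insufficient", and the investigator also judges the patient unsuited to the treatment. Criterion (1) covers adverse events; (2) and (3) cover the subject's request and personal circumstances.
- **Sample size (section 2.4).** Each subgroup needs 25 patients for 90% power. "Assuming a 20% dropout rate during the study period", the target becomes 32 per subgroup and 64 overall.
- **Other time points (section 2.12).** For secondary items 1, 4 and 6 to 11, "Summary statistics of the measured values and changes from baseline will be calculated for each time point". Item 10 is the change in JPAC-QOL overall and subscale scores.

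**The concern.** A paired t-test takes one difference per patient, so a patient without a week-12 score adds nothing unless a rule supplies a value. The article states no such rule. On its face, the analysis set named (FAS) and the patients who can enter the test (those with both scores) therefore differ.

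The difference need not be harmless. One of the protocol's own routes out of the study is a poor result on linaclotide. If such patients leave before week 12 and only observed pairs are analysed, the patients who remain are a favourable selection.

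In a single-arm study the mean change and its CI are the result, and no control arm suffers a similar loss. Section 2.4 also treats efficacy equivalent to or better than that in an earlier elobixibat study as clinically meaningful, so the size of the estimate matters as well as the p-value.

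**Working it through.** **1. The plan's own figure.** Inputs from section 2.4: mean change -0.46, SD 0.68, two-sided 5%, power 90%, dropout 20%. Exact paired t-test power (noncentral t, noncentrality = 0.46/0.68 × √n):
- n = 24: 88.7%
- n = 25: 90.05%

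So 25 is right. Then 25/(1 − 0.20) = 31.25, rounded up to 32, and 2 × 32 = 64. The stated size reproduces. The planning arithmetic counts dropouts as giving no data to the test.

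**2. Who can enter the test.** With 20% of 64 missing, about 0.8 × 64 = 51 patients have both scores. Power at the planned effect with n = 51 is 99.7%.

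**3. Size of a possible bias.** The article gives neither the dropouts' outcomes nor the share lost for poor response, so the dropout mean m and the rate d are assumptions:

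all-treated mean = (1 − d) × (−0.46) + d × m

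| d | m | All-treated mean | Observed-pairs mean minus all-treated | Ratio |
|---|---|---|---|---|
| 0.20 | -0.46 (like completers) | -0.460 | 0 | 1.00 |
| 0.20 | -0.20 | -0.408 | -0.052 | 1.13 |
| 0.20 | -0.10 | -0.388 | -0.072 | 1.19 |
| 0.20 | 0 (unchanged) | -0.368 | -0.092 | 1.25 |
| 0.20 | +0.20 (worse) | -0.328 | -0.132 | 1.40 |
| 0.10 | 0 (unchanged) | -0.414 | -0.046 | 1.11 |

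Example: 0.8 × (−0.46) + 0.2 × 0 = −0.368, and 0.46/0.368 = 1.25.

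**4. Significance at the planned effect.** Take 20% dropouts with mean change 0.
- Each dropout scored exactly 0: SD = √[0.8 × (0.68² + 0.46²) − 0.368²] = 0.635. Power is 99.5% for 64 patients and 88.7% for 32.
- Dropouts spread around 0 with SD 0.68: SD = √[0.68² + 0.8 × 0.2 × 0.46²] = 0.704. Power is 98.4% for 64 and 81.7% for 32.

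The overall test stays well powered. The subgroup tests fall somewhat below the planned 90%.

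**5. No true change.** In simulations of 20,000 trials of 64 patients with true mean change 0 and 20% missing, the two-sided false-positive rate was 5% when missingness was unrelated to outcome. It was about 11% when the log-odds of missingness rose by 0.5 per SD of worse change, and about 25% when they rose by 1.0. With 10% missing, the last two figures were about 7% and 11%. These log-odds are assumptions.

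**6. Whether the PPS would show it.** The PPS is a subset of the FAS and requires the primary endpoint. A patient without that value is in neither comparison, so agreement between FAS and PPS says nothing about those who are missing. PPS criteria (1) and (5) also fit together for a patient who stops before day 42 only if that patient can still have a primary value. The article does not say where it would come from.

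**The case against.** A reader might infer that the plan restricts the primary test to completers and that the effect will be overstated by 13 to 25%. The documents do not support that as fact.

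- **No sentence limits the test to observed pairs.** The rule for a missing score may stand in the full protocol or SAP, which are not shown.
- **The PPS exemption points partly the other way.** It suggests that an early stopper may have a primary value, for example from a discontinuation assessment or a carried-forward score. The visit schedule (Table 2) is not shown, so this cannot be checked.
- **The inflation from 25 to 32 is a planning allowance, not an analysis rule.** The 20% might also include patients who enrol at visit 1 and fail the medication initiation criteria at visit 2. They never take linaclotide and so lie outside the FAS.
- **Removal under 2.7(5) is discretionary.** Rescue medication and the dose adjustments in section 2.6 give patients with a poor response or diarrhoea ways to stay in the study, and other reasons for leaving need not follow the score.
- **A mixed model is no complete cure.** It assumes data missing at random, given the scores that were recorded, and helps only where interim JPAC-QOL scores exist. The wording on time points covers many items and does not prove that they do.

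All of this stands, and it makes the bias conditional and its size uncertain. It does not remove the point. The named test needs both scores, the FAS does not secure the second one, the protocol allows its loss for poor response, and the one stated robustness check cannot detect the consequence.

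**Conclusion.** The point holds in conditional form. Followed as written, the primary analysis yields an observed-pairs estimate, and loss for poor response would push it towards benefit. At 20% treated dropout and a completer mean of -0.46, the overstatement is nil if dropouts change like completers, about 0.05 points if they change by -0.2, and about 0.09 points if they are unchanged. At 10% dropout with no change in the dropouts, it is about 0.05.

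If the planned effect is real, what is at stake is the estimate and its CI, not overall significance. The raised false-positive rates arise only if there is no true change and missingness follows outcome, so they are no forecast for this trial.

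Severity is moderate: the study is exploratory and single-arm, and the article itself names the lack of randomisation and the small sample as limitations. The inconsistency between PPS criteria (1) and (5) needs resolving in any case.

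**What to change.** 1. State how FAS patients without a week-12 JPAC-QOL score enter the primary analysis.
2. Pre-specify a sensitivity analysis in all FAS patients that sets those who stopped for insufficient response, worsening or an adverse event to no change from baseline. Report the mean change and 95% CI beside the primary result.
3. Where interim JPAC-QOL scores are collected, estimate the week-12 mean change and 95% CI with a mixed model for repeated measures on all post-baseline scores, with visit, baseline score and abdominal-symptom stratum as fixed effects. Keep the paired t-test as the supportive observed-case analysis. If there are no interim scores, keep the t-test and rely on item 2.
4. Reconcile PPS criteria (1) and (5): say whether a patient who stops before day 42 for inadequate response has a primary value and at which assessment it is obtained.
5. Report the number of FAS patients without a week-12 score, by reason for stopping.

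Cost: wording and a little extra programming, with no new data. The estimate may be slightly less favourable, and under the no-change analysis the subgroup power may fall below 90% (about 89% with 20% scored as zero), while overall power stays above 99%.

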### Data management and monitoring

2.13

A study subject identification code will be assigned when the patients are enrolled. The study subject identification code consists of a numerical code or other symbols unrelated to information that can help identify specific individuals, such as their initials or medical record IDs. The information will be anonymized using the study subject identification code when preparing documents related to this study, such as case registration forms and report forms (CRF). The principal investigator will prepare a correspondence list containing information such as the name and medical record ID of the study subjects so that they can be identified from the anonymized information as necessary. This information will be strictly stored and managed so that it is not leaked. Additionally, the principal investigator strictly will store and manage consent forms, medical records, examination data, patient diaries, and medical questionnaires in a lockable storage room at each facility. Electronically stored data in an electromagnetic storage device, such as a PC or USB memory stick that is independent of the hospital LAN or the Internet, will be password-protected, stored, and managed strictly in a lockable storage facility when not in use.

The CRF used in this study will be stored in the EDC system (VIEDOC™, Viedoc Technologies AB, Uppsala, Sweden). The principal investigator will submit the CRF by entering the data into the EDC system immediately after the completion of the examination and observation of each subject.

Monitoring will be outsourced to an external agency and planned accordingly.

## Discussion

3

This is the first study to evaluate the efficacy and safety of switching to linaclotide in patients with CIC or IBS-C who are taking MgO and show an inadequate response. In Japan, the Ministry of Health, Labour, and Welfare recommends the use of linaclotide after the use of conventional laxatives with inadequate efficacy (https://kouseikyoku.mhlw.go.jp/shikoku/iryo_shido/000072356.pdf). However, no studies on the efficacy or safety of linaclotide as a second-line treatment for CIC or IBS-C have been conducted yet. Additionally, the clinical trial of linaclotide that preceded the present study included a large number of young patients. For example, Fukudo et al. report the efficacy of linaclotide in patients with chronic constipation, wherein the mean age of the subjects was 42.7 years (±11.7 SD) and 3.4% of all subjects were over 65 years [11]. In Japan, linaclotide is started at 0.5 mg. In a randomized controlled trial where low-dose linaclotide was administered orally for chronic constipation, the mean age of the subjects was less [7,12]. The morbidity associated with chronic constipation increases with age [2]. Patients with IBS have a lower average age than patients with CIC, and the prevalence of IBS is approximately 10% with IBS-C accounting for approximately 20–30% of these patients [13]. Considering that the reported prevalence of CIC is 14% [14], it is likely that the prevalence of IBS-C will be lower than that of CIC and the overall age of the patients will be relatively high in this study, as many elderly people with a diagnosis of CIC will be included in the study. Therefore, these trials have discrepancies in clinical practice. Since this study is expected to attract more elderly patients and patients with underlying diseases as compared to previous clinical trials, we believe that the data gap between clinical trials and clinical practice will be eliminated, thus providing efficacy and safety data in patients that are similar to those in actual clinical practice.

In an internet survey of patients with chronic constipation in the U.S. and Japan, many respondents reported abdominal symptoms, with abdominal discomfort and bloating being the most bothersome symptoms [15,16]. Epidemiological studies conducted in the U.S. and Japan have also reported that patients with chronic constipation have reduced health-related quality of life (SF-12v2) and labor productivity as compared to healthy individuals [3,17]. Studies involving patients with IBS-C and CIC have also shown that of the large number of patients treated with over-the-counter and prescription drugs, many are not satisfied with their effectiveness and suffer from inadequate efficacy and side effects such as diarrhea [18,19]. The results of these previous studies suggest that constipation symptoms perceived as bothersome, such as abdominal bloating, may reduce the quality of life of patients with CIC and IBS-C. Furthermore, as linaclotide administration may lead to changes in patients’ symptoms and alter their quality of life, quality of life is considered the primary endpoint of this study. The Patient Assessment of Constipation Quality of Life Questionnaire (PAC-QOL), developed to assess the impact of constipation symptoms on quality of life, is widely used internationally as a standard disease-specific measure for chronic constipation. In addition, PAC-QOL has been used in studies that have included patients with IBS-C [20]. In Japan, the reliability and validity of the Japanese version of the PAC-QOL (JPAC-QOL) have been evaluated [21,22]. However, the only drug developed using JPAC-QOL in Japanese clinical trials for the treatment of chronic constipation is elobixibat; linaclotide has no JPAC-QOL data for the quality of life [8,23]. Therefore, JPAC-QOL is considered the primary endpoint in this study.

The strengths of this study are that it is the first to use linaclotide as a second-line treatment for MgO and is expected to provide data closer to clinical practice as a large proportion of elderly patient enrollment is anticipated. The limitations of this study are that it is an exploratory trial instead of a randomized trial, and the sample size is small.

